| **Statistical Considerations:** | **Primary Endpoint:**  The primary outcome (proportion of patients with PSMA-positive pathological lesions = patient based sensitivity) will be compared between tracers using an absolute risk difference (new tracer minus old tracer) with a one-sided lower 95% confidence interval for paired proportions (Wald with Bonett–Price Laplace adjustment). If the lower limit lies above -10%, we will claim non-inferiority. Detection rates per patient will be based on majority consensus reads.  **Secondary Endpoints:**   - Parametric imaging will be performed for the two radiotracers in a subset of patients (n=10*), allowing comparison of the tracers’ dosimetric and kinetic parameters, with affinity for the PSMA radioligand by calculation of the parametric equilibrium constant *K*_D,_ which will be compared between the two tracers with descriptive statistics. - The number of PSMA-positive lesions defined as pathological, benign and uncertain per region will be compared using mixed-effects Poisson regression. Patient-level data will also be analysed using the Wilcoxon signed-rank test.. - Inter-reader reliability will be compared on the region level using Krippendorff’s alpha for benign, pathological and uncertain lesions, separately for the two tracers. - Region based PPV will be calculated for each tracer separately with 95% Wilson score confidence intervals. The two tracers will be compared using McNemar’s test and an absolute risk difference with 95% confidence interval. - Semi-quantitative tumour to background ratio (defined as lesion SUV ÷ SUV of reference background region, where the background uptake is defined by convention as the left gluteal musculature) will be summarised on a region-level (i.e. using the mean over all positive lesions per region). Summarised data will be analysed using linear mixed-effects regression models. - The number and severity of adverse event will be analysed using descriptive statistics. All serious adverse events will be listed.   *The requirement for N=10 patients is justified on the previous dosimetry paper for the established PET radiotracer ^68^Ga-PSMA-11 which was adequately powered to demonstrate a mean-effective dose of 0.023 ± 0.004 mSv/MBq, i.e. with a precision in the µSv range [1]. |

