Finally, the application of the radiotracer into the same patient allows for a comparison of tracer kinetics. Although radiotracer kinetics are well known from the original pioneering dosimetric publications [1], they have never been compared in a head to head fashion. Obtaining dynamic scans over the first hour post injection will allow intra-individual dosimetry and a head-to-head comparison of parametric imaging parameters, allowing a direct comparison of the radiotracer’s affinity using standard parametric imaging techniques [16].

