### Parametric Imaging Protocol

For a subset of patients willing to undergo additional examination, (n=10), images will be acquired for ca. the first hour post injection of radiotracer in addition to the standard exam at 2h. Instead of the patient waiting on a chair for the hour(s) after injection, the radiotracer is applied while the patient lies on the scanner, which passively collects data regarding the tracer’s distribution in real-time. From this, parametric (dynamic) data can be obtained, including (for the first time) an intra-individual comparison of tracer dynamics and ligand binding to tumours.

The parametric scans result in no additional radiation dose, except for an additional low-dose CT scan for attenuation correction (1mSv). The examination otherwise remains the same. After one hour, the patient waits as per clinical routine in the waiting area, and the clinically indicated scan is performed at the appointed time (2h p.i.). A separate consent form detailing these extra procedures has been provided.

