## Risks / Benefits

### Risks

Given that the new tracer is now in routine clinical use in Switzerland and world-wide, no risk in terms of poor diagnostic performance can be anticipated from either radiotracer. Any additional radiation exposure entailed is within appropriate limits as defined by the FOPH (<20 mSv). The small risk of cancer induced by the radiation must be considered to be minimal for an aged population with a known cancer diagnosis undergoing examination for medical benefit.

Concerning the excellent safety profile of the radiopharmaceuticals, we draw particular attention to the relevant paragraph of the “Fachinformation”, for example for ^68^Ga-PSMA-PET/CT, which we quote here in the original German:

«Die ^68^Ga-PSMA-PET/CT ist mit einer geringen Strahlenexposition verbunden, die etwa der ein- bis zweifachen jährlichen natürlichen Strahlenexposition entspricht (ca. 3-6 mSv). Sie liegt unter der Strahlendosis der meisten konventionellen CT-Untersuchungen. Akute und/oder chronische Strahlenschäden durch ^68^Ga-PSMA-11 sind nicht zu erwarten oder je beobachtet worden. »

Furthermore, worldwide use of PSMA-ligands, including prospective phase II single arms trials (for ^68^Ga-PSMA-11 [20]), have reported no adverse safety events [25]. We highlight the fact that radiopharmaceuticals used as tracers are given in sub-pharmaceutical doses and no pharmaceutical effect is anticipated. The examination is routinely performed in men of advanced age with a known cancer diagnosis for medical benefit.

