## Secondary Outcomes

- Intra-individual comparison of the parametric imaging parameter K*_D_* (measure of tracer affinity) for the two radiotracers for n=10 patients.
- The number of pathological, benign and uncertain lesions for each tracer in five regions (prostate bed, pelvic lymph nodes, extra-pelvic lymph nodes, bone, or other organs) classified by six blinded readers (three for each tracer) using previously published interpretation guidelines (PSMA-Rads 1.0)
- Inter-reader reliability between the three readers for each tracer on the level of the region with respect to three categories (pathological, benign, uncertain).
- The region-based positive predictive value (PPV), i.e. the percentage of pathological lesions that are confirmed pathological at the 6 month follow-up (based on the subset of patients and lesions with follow-up data at 6 months).
- Tumour visibility will be compared by means of uptake values (SUV) as well as tumour to background contrast in a lesion based analysis. The tumour to background ratio (TBR) is defined as lesion SUV and SUV÷ SUV of reference background region, where the background uptake is defined by convention as the left gluteal musculature.
- Number and severity of adverse events per tracer (up to 48h follow-up, see below)

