Acquisition of imaging at time-points less than 1h p.i. is not recommended in PSMA-ligand PET due to the limited tracer uptake by PC lesions [21, 22], which is known to increase with time for PSMA-ligands [22, 23]. This pharmacokinetic property favours later acquisition, particularly in cases of diagnostic uncertainty [29]. However, we consider the acquisition of images at time-points later than 2h to be impractical due to the short half-lives of the radiopharmaceuticals which requires much larger initial doses of the radiopharmaceutical or significantly longer acquisition times [17]. As such, we compare both tracers at an equivalent time point, with 2h chosen. Given that the radiotracer will be administered only once, and a low dose CT is used for attenuation correction, our proposed protocol ensures that the total radiation exposure for the individual is kept to the lowest practicable level.

***Fig 3.*** *A lesion in the superior prostatic fossa is visible in the bottom row (post forced diuresis, 68Ga-PSMA-11 PET/CT), but indistinguishable from the bladder activity in the top row (without diuresis) in the same patient. Image courtesy of principal investigator*.

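### The first secondary endpoint names absolute affinity (K_D), but one tracer-mass dynamic scan per tracer can give at most a relative binding ratio, and only under conditions the protocol does not state

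*Protocol*

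**What the plan says.** The synopsis, under Statistical Considerations, describes a ten-patient parametric imaging subset "allowing comparison of the tracers’ dosimetric and kinetic parameters", in which affinity is to be obtained "by calculation of the parametric equilibrium constant" K_D. Section 5.2 makes this the first secondary outcome: "Intra-individual comparison of the parametric imaging parameter K" with subscript D, glossed there as a measure of tracer affinity. The synopsis list of outcomes says the same.

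On the data to be collected:

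- Section 3.5.1: "images will be acquired for ca. the first hour post injection of radiotracer in addition to the standard exam at 2h".
- Section 6.1.2.1: the dynamic acquisition runs from injection to 80 min.
- Section 6.1: the tracer is given once per examination.
- Section 3.7.1: "radiopharmaceuticals used as tracers are given in sub-pharmaceutical doses".

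No scan at a second ligand mass, no blocking scan and no independent measure of receptor density is described. Section 9.2.2 refers to standard software and descriptive statistics only.

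On dosimetry, section 3.1 states: "Obtaining dynamic scans over the first hour post injection will allow intra-individual dosimetry". Dosimetry also appears in the synopsis sentence above, but is not in the list of outcomes.

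**The concern.** An equilibrium dissociation constant is a property of the ligand and its target. To separate it from the amount of target present, the data must contain some information on saturation: several ligand masses, a blocking study, or a separate estimate of receptor density. The design has none of these. An unseen analysis plan could add a model and a formula, but it could not add information that the acquisition does not produce.

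At stake is what the trial may claim. A K_D reported for each tracer would be read as affinity, although its value also carries receptor density. Even a difference between tracers could partly reflect plasma binding, delivery or trapping. Ten patients accept longer scanning and an extra low-dose CT of 1 mSv per dynamic examination (sections 3.5.1 and 8.2.2) for this endpoint, so it should be one that the scans can deliver.

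**Working it through.** **The plan's own figure.** The synopsis justifies n = 10 by an earlier effective dose of 0.023 ± 0.004 mSv/MBq. Reading 0.004 as a standard deviation, the standard error is 0.004/√10 = 0.0013 and the 95% half-width is 2.262 × 0.0013 = 0.0029 mSv/MBq. That fits the stated µSv precision, and 150 MBq × 0.023 = 3.45 mSv fits the 3.5 mSv in section 8.2.2. It concerns effective dose and says nothing about how well K_D can be estimated.

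**Step 1: what one tracer-mass scan contains.** In a two-tissue model with saturable binding, k3 = k_on × (Bmax − B) and k4 = k_off, where B is the bound amount. At tracer mass B is far below Bmax, so k3 ≈ k_on × Bmax and

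k3/k4 ≈ Bmax × k_on/k_off = Bmax/K_D.

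K_D enters only through this ratio.

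**Step 2: numerical check.** The rate constants are assumed, not taken from the protocol: K1 = 0.2, k2 = 0.3, k_on = 0.001, k_off = 0.01, with base values Bmax = 100 and K_D = 10. Curves were computed for 0–80 min plus a point at 120 min, with Bmax/K_D held fixed.

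| K_D | Bmax | Largest relative difference from base, tracer mass | Same, 1000 times the mass |
|---|---|---|---|
| 5 | 50 | 0.0023% | 2.3% |
| 20 | 200 | 0.0011% | 1.1% |
| 50 | 500 | 0.0018% | 1.8% |
| 100 | 1000 | 0.0021% | 2.1% |

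At tracer mass a twentyfold range of K_D cannot be told apart. The curves start to separate only when the mass rises.

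**Step 3: what pairing adds.** For one lesion imaged with both tracers,

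(k3/k4) for 18F ÷ (k3/k4) for 68Ga = K_D for 68Ga ÷ K_D for 18F,

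provided that Bmax is the same on both days, k4 is above zero and estimable, and non-specific terms are comparable. The gap of 2 to 14 days and the requirement of unchanged prostate cancer treatment (section 7.1) support the first condition. The second is doubtful on the protocol's own account: section 6.1 discourages scans before 1 h "due to the limited tracer uptake by PC lesions" and expects lesion uptake to go on rising, which points to slow release. In an illustrative simulation with an 80 min dynamic scan plus the 2 h point, a noise-free input function and 5% frame noise, the 95% range of the estimated k3/k4 relative to its true value was:

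- 0.5 to more than 100 with k4 = 0.002/min (curve still rising at 2 h);
- 0.8 to 1.4 with k4 = 0.01/min (plateau before 2 h).

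**Step 4: dosimetry.** The share of decays after time t, by physical decay alone, is 2^(−t/T). T = 68 min for 68Ga (section 3.1). The protocol gives no half-life for 18F; 110 min is assumed.

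| | after 60 min | after 80 min | after 120 min |
|---|---|---|---|
| 68Ga | 54% | 44% | 29% |
| 18F | 69% | 60% | 47% |

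Suppose decay-corrected activity is flat to 2 h and then clears with biological half-life Tb. With Te = 1/(1/T + 1/Tb), extrapolating by physical decay alone overstates time-integrated activity by 1/[1 − 2^(−120/T) × (1 − Te/T)] − 1. At Tb = 60 min:

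- 68Ga: Te = 31.9 min; 1/(1 − 0.294 × 0.531) − 1 = 19%.
- 18F: Te = 38.8 min; 1/(1 − 0.469 × 0.647) − 1 = 44%.

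With no biological clearance both are 0%. The possible error therefore runs from 0 to 19% for 68Ga and from 0 to 44% for 18F.

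**The case against.** The best reply is that the endpoint is a within-patient comparison. Receptor density is common to both scans of a lesion, so the scaling of Bmax and K_D together in Step 2 is not the contrast the trial will report. This stands in part: a relative K_D is obtainable under the conditions in Step 3. But the protocol names K_D, not a ratio, and does not state those conditions.

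A second reply is that K_D may be meant as an apparent parameter produced by standard software, with the model left to an analysis plan. Leaving the model to that plan is acceptable. Calling the result an equilibrium constant and a measure of affinity is not, unless it is qualified.

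Three stronger readings are tempting and are not supported:

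- **That any K_D comparison would be uninterpretable.** Pairing removes receptor density, and the rest depends on assumptions that can be stated and examined.
- **That the lack of planned blood sampling rules out kinetic modelling.** An image-derived input function is possible.
- **That dosimetry cannot be done because only one hour of data exists.** Section 3.5.1 adds the 2 h scan and section 6.1.2.1 runs the dynamic scan to 80 min, so an extrapolated estimate is possible.

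**Conclusion.** The point holds for absolute K_D: the stated endpoint is not identifiable from the data the protocol describes. This follows from the structure of the model and does not depend on the illustrative rate constants. A relative binding ratio is possible but conditional, and the expectation of rising uptake makes k4 the weak link; how weak depends on rate constants and noise that the protocol does not give. The dosimetry promise is an imprecision, not an impossibility. Its size depends on the assumed 18F half-life and on clearance after 2 h, and the possible error differs between tracers, which matters for a head-to-head comparison.

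The descriptions of the dynamic window also disagree: about one hour in sections 3.1 and 3.5.1, 80 min in section 6.1.2.1.

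The consequence is limited. The sub-study has ten patients and is descriptive (section 9.2.2), and section 11.4.2 calls it exploratory and without influence on trial conduct. A reader should not infer any effect on the non-inferiority conclusion. The wording should be changed because the claim is a named endpoint and the correction is cheap.

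**What to change.** 1. In the synopsis (Outcomes and Statistical Considerations) and section 5.2, replace K_D with parameters the scan supports: the net influx rate Ki and K1 to k3 from a stated model, with an image-derived input function, the same frames for both tracers and the 2 h scan as a late point. Report the within-lesion ratio of k3/k4 between tracers only where k4 is identifiable, with its assumptions.
2. Describe the results as uptake kinetics or apparent relative binding, not as absolute affinity, and align section 3.1 with this.
3. Reconcile the stated length of the dynamic acquisition across sections 3.1, 3.5.1 and 6.1.2.1.
4. In the synopsis and section 3.1, either drop the dosimetry promise or label it an extrapolated estimate that includes the 2 h scan, with the extrapolation rule stated for both tracers.

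The cost is wording in the protocol and analysis text; no scan, dose or sample is added. The trial gives up the claim to compare absolute affinity.

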### Study Calendar

| **Step** | **Pre Study**  **-7-14 days** | **Examination 1**  **Day 0** | **Examination 2**  **Day 2 -14** | **Examination 2 + 10 days** | **Post examination**  **Month 6 +** |
| --- | --- | --- | --- | --- | --- |
| Informed Consent | X |  |  |  |  |
| Demographics | X |  |  |  |  |
| Medical history | X |  |  |  |  |
| Randomisation to group A or B | X |  |  |  |  |
| Scan 1 (radiotracer determined by group, see study procedures) |  | X |  |  |  |
| Scan 2 (radiotracer determined by group, see study procedures) |  |  | X |  |  |
| Analysis of parametric imaging data (first ten patients only) |  |  |  | X |  |
| Clinical record analysis*  Follow up consists of an analysis of the patient’s clinical records for treatment post scan and is performed 6 months following Examination two. |  |  |  |  | X |
| Data analysis |  |  |  |  | X |

## Laboratory

No laboratory is associated with this trial.

## Monitoring institution

Monitoring will be carried out by a monitoring team from the clinical trials unit (CTU) Bern.

## Data Safety Monitoring Committee

Dr. med. [name] along with the trial statistician will form a data safety monitoring committee and report to the PI any data safety issues. The committee is independent from the Sponsor and free from competing interests. The monitoring committee is supported by the trial study nurse..

# ETHICAL AND REGULATORY ASPECTS

Before the study is conducted, the protocol, the proposed patient information and consent form as well as other study-specific documents shall be submitted to a properly constituted Competent Ethics Committee (CEC) and/or competent authorities (Swissmedic and/or FOPH). The decision of the CEC, FOPH and Swissmedic concerning the conduct of the study will be made in writing to the Sponsor before commencement of this study. The clinical study can only begin once approval from all required authorities has been received. Any additional requirements imposed by the authorities shall be implemented.

## Study registration

The study is registered with ClinicalTrials.gov NCT05079828 (National Institutes of Health, USA). In addition, the study will be registered in a national language in the Swiss National Clinical Trials Portal (SNCTP via BASEC).

## Categorisation of study

The radiopharmaceuticals ^68^Ga-PSMA-11 and ^18^F-PSMA-1007 are authorised for use in Switzerland and used in accordance with the prescribed indication. The categorisation is Category C. We note the following:

1. The indication is within the same disease group of the International Classification of Diseases (ICD) (C61 Malignant neoplasm of prostate)

2. The authorised pharmaceuticals ^18^F-PSMA-1007 and ^68^Ga-PSMA-11 are used in accordance with the standard described in guidelines prepared in accordance with internationally accepted quality criteria (“Fachinformation”).

The clinically indicated scans will be performed using tracers which are both permitted for use in Switzerland by the regulatory authorities [2, 3] and will be used strictly in accordance with their prescribed indication. The total radiation dose per investigation is significantly below 20mSv.

## Competent Ethics Committee (CEC)

The sponsor and principal investigator are responsible for ensuring CEC authorisation prior to commencement of this study.

All changes in the research activity and all unanticipated problems involving risks to humans, including a planned or premature study end, will be reported, and the final report will be submitted to the appropriate committee. No changes will be made to the research protocol without prior CEC approval, except where necessary to eliminate apparent immediate hazards to study participants.

Premature study end or interruption of the study is reported within 15 days. The regular end of the study is reported to the CEC within 90 days, the final study report shall be submitted within one year after study end. Amendments are reported according to chapter 2.10.

## Competent Authorities (CA)

This application for a Category C study using radiopharmaceuticals will be submitted in parallel to Swissmedic and to the Federal Office of Public Health in accordance with §28 ClinO.

Reporting duties and timelines are the same as for the CEC, except for non-substantial amendments, which shall be reported as soon as possible. Amendments are reported according to chapter 2.10.

## Ethical Conduct of the Study

The study will be carried out in accordance to the protocol and with principles enunciated in the current version of the Declaration of Helsinki, the guidelines of Good Clinical Practice (GCP) issued by ICH, the Swiss Law and Swiss regulatory authority’s requirements. The CEC and regulatory authorities will receive annual safety and interim reports and be informed about study stop/end in agreement with local requirements.

## Declaration of interest

The sponsor, principal investigator and team declare no conflicts of interest.

## Patient Information and Informed Consent

The initial examination, irrespective of the tracer used, is performed as part of the routine treatment of the individual. Examinations with both tracers are performed many times per day at multiple centres in Switzerland. The initial examination, irrespective of tracer type, is reimbursed by the individual’s health insurance in accordance with Swiss health insurance regulations.

Before the initial investigation, the investigators will contact each individual by telephone to explain to each participant the nature of the study, its purpose, the procedures involved, the expected duration, the potential risks and benefits and any discomfort it may entail. Each participant will be informed that the participation in the study is voluntary and that he may withdraw from the study at any time and that withdrawal of consent will not affect his subsequent medical assistance and treatment.

The participant will be informed that his medical records may be examined by authorised individuals other than their treating physician.

All participants for the study will, in advance of informed consent being obtained by means of a face-to-face meeting (i.e. “Aufklärungsgespräch”), be provided with a participant information sheet and a consent form describing the study and providing sufficient information for participants to make an informed decision about their participation in the study. The information will be provided to the patients at least 24h in advance of being randomised to the first study. Patients can withdraw from the study at any time point and without prejudice to their treatment.

By adhering to this procedure, no delay will be incurred on the part of the patient in the scheduling of his examination, and a minimum of 24 hours is provided for the patient to consider whether he wishes to participate.

The formal consent of a participant, using the approved consent form, will be obtained before the participant is entered into the trial. The consent procedure will involve a face-to-face discussion with a medically qualified investigator. The form will be signed by the investigator “Prüfarzt” (or his designee) and patient.

The participant should read and consider the statement before signing and dating the informed consent form and should be given a copy of the signed document. The consent form must also be signed and dated by the investigator (or his designee), and it will be retained as part of the study records.

The patient can withdraw his consent at any time.

